### Frozen-thawed embryo transfer

During the subsequent menstrual cycle, the same endometrial preparation regimen will be used as in the previous cycle. When the endometrial thickness is adequate, with serum progesterone level less than 1.5 ng/mL, the same regimen for luteal phase support (vaginal progesterone gel 90 mg daily and oral dydrogesterone 10 mg twice daily) will be added.

Participants in both arms will receive frozen-thawed single euploid blastocyst transfer. Serum human chorionic gonadotropin (hCG) levels will be measured 12–15 days after embryo transfer. If pregnancy is confirmed, luteal progesterone support will be continued until 10–12 weeks of gestation. All conceptions will be followed through the end of pregnancy.

### Discontinuation criteria

Reasons for dropping out of the trial are as follows:Participants become pregnant spontaneouslyParticipants with no viable embryos for transfer after thawingParticipants who request to withdraw from the clinical trial

### Outcome and outcome assessments

#### Primary outcome

The primary outcome is live birth after frozen-thawed euploid blastocyst transfer, defined as the delivery of any newborns with signs of life at or beyond 28 weeks of gestation.

#### Secondary outcomes

The secondary outcomes include biochemical pregnancy, clinical pregnancy, implantation, ongoing pregnancy, and pregnancy loss. Biochemical pregnancy is defined as serum β-hCG level ≥ 10 mIU/mL measured 12–15 days after embryo transfer. Clinical pregnancy is defined as the detection of an intrauterine gestational sac via transvaginal ultrasound 35 days after embryo transfer. The implantation rate is calculated as the total number of intrauterine gestational sacs detected by transvaginal ultrasound divided by the total number of embryos transferred. Ongoing pregnancy is defined as a pregnancy beyond 12 weeks of gestation confirmed by a gestational sac with fetal heart activity using ultrasound.

#### Follow-up protocol

The first follow-up is at 12 weeks of gestation. Complications in the first trimester of pregnancy (including but not limited to spontaneous abortion, ectopic pregnancy, gestational trophoblastic disease, vaginal bleeding, or hyperemesis gravidarum) will be recorded by reviewing medical records or by telephone.

The second follow-up time point will be at delivery. The delivery information (including but not limited to gestational age, delivery mode, placenta abnormalities, or delivery complications) and neonatal information (including gender, birth weight, birth defects) will be obtained by standardized case report forms (CRFs) or by reviewing obstetric and neonatal medical records.

Participants will receive standard maternity care as per usual practice in addition to the study follow-up. Adverse events and concurrent drugs will be collected and documented at each visit throughout the trial. Participants who drop out or are lost to follow-up will be recorded.

### Adverse events

Adverse events (AEs) are defined as any untoward medical occurrences that arise during the trial period, whether or not they are thought to be related to the study intervention. Serious adverse events (SAEs) refer to any events that occur during the subject’s participation in this trial that meet one or more of the following criteria: death, life-threatening conditions, serious or persistent disability, necessitating inpatient hospitalization or extending an existing hospitalization, neonatal death up to 42 days after delivery, congenital abnormality or birth defect, or be otherwise deemed serious assessed by the principal investigator.

All AEs and SAEs will be thoroughly evaluated and recorded. Within 5 days, all SAEs will be reported to the principal investigator. Unexpected SAEs and SAEs that are possibly related to the study intervention should be reported within 24 h to the principal investigator. Upon receiving the report, the principal investigator will assess the seriousness and potential causality of the event in relation to the study intervention. Subsequently, any SAE will be reported to the ethics committee of Ren Ji Hospital, Shanghai Jiao Tong University School of Medicine, and DCC. Appropriate medical care and follow-up will be provided to the affected participant as per standard clinical practice. The principal investigator will maintain documentation of the SAE, including the initial report and any actions taken in response. If any SAE occurs and is thought to be related to the study intervention, 24 h unblinding will be available through the DCC for the individual participant if this is required by the principal investigator.

### Data management

Before the trial begins, all of the investigators, including physicians, nurses, and research assistants, will participate in a training course to ensure an understanding of the study protocol, the accuracy of outcome assessments, and the data collection. For each investigator, a protocol and standard operating procedures will be provided. All the research data will be collected using standardized CRFs where participants’ private information cannot be traced. The DCC is responsible for monitoring the trial. The DCC staff will routinely check the veracity, accuracy, and integrity of the data, to ensure the quality of the data collected.

### Data analysis plan

The data will be analyzed using SPSS (version 26.0, IBM Corp, Armonk, NY). Normally distributed continuous variables will be presented with mean ± standard deviation (SD), while non-normally distributed continuous variables with median and interquartile ranges (IQR). Independent samples *t*-tests or Wilcoxon’s rank sum test will be used to test the between-group differences as appropriate. Categorical variables will be presented with frequency and percentage. The Pearson chi-square and Fisher’s exact tests will be used to test the between-group differences as appropriate. A two-sided alpha level of 0.05 will be considered statistically significant.

The primary analysis will be conducted according to the intention-to-treat (ITT) principles. The primary outcome, live birth rate, will be compared between the two groups using the Pearson chi-square test. Women lost to follow-up will be considered as not having had a live birth. Secondary outcomes, including rates of biochemical pregnancy, clinical pregnancy, implantation, ongoing pregnancy, and pregnancy loss, will be analyzed using the Pearson chi-square test or Fisher’s exact test as appropriate. Secondarily, a per-protocol analysis will be performed among participants who complied with the trial protocol.

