### Sample size

Previous researches demonstrated that compared to sET, pET guided by ERT could increase pregnancy rates by about 25% in women with RIF [19, 27]. According to the retrospective data of our center, live birth among women with RIF following frozen-thawed euploid embryo transfer is approximately 35%. In the present study, we assume that the live birth rate will be improved from 35% in the sET arm to 60% in the pET arm.

For the sample size estimations, we will use a 2-tailed test with a statistical significance set at *α* = 0.05 and a statistical power of 1 − *β* = 0.80. The ratio between groups will be 1:1. Therefore, we need to include at least 118 women (59 women in each arm). Taking into consideration a dropout rate of 10%, we expect to include a total of 132 enrollees (66 enrollees in each arm).

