### Randomization and blinding

All eligible women will be randomly assigned to one of two study arms according to a computer-generated dynamic block randomization sequence (sized 2, 4, and 6). The randomization sequence is generated by biostatisticians in the data coordinating center (DCC) using the SAS software version 9.2 (SAS Institute, Cary, NC) and has been input into an online randomization system by the DCC staff members prior to initiation of the study. The sequence will be kept strictly confidential by the DCC staff, thus to ensure that the study investigators are all blinded to the upcoming group allocation. On the day of endometrial biopsy, authorized investigators will log in to the password-protected account to get allocation information for eligible subjects. This is a single-blind clinical trial since it is not feasible to blind the doctors. Group allocation and ERT results will not be disclosed to all study participants.

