### Screening

At the screening visit, all participants will be made aware of the trial and study plan. Eligible couples who are interested will sign a written informed consent and complete a comprehensive medical history review, physical examination, and pelvic ultrasound. The history of previous fertility treatments (including ovarian stimulation, oocyte retrievals, embryo transfers, hysteroscopy, and history of chronic endometritis) will be recorded. When necessary, screening for immunological and thrombophilic factors and chronic endometritis will be recommended.

Safety assessment includes but not limited to complete blood count (CBC), liver and renal function, fasting blood glucose, and blood pressure. Figure 2 (SPIRIT diagram) is a schedule of the study process including enrollment, interventions, and assessment. This protocol refers to the SPIRIT Reporting Guidelines [28], and the SPIRIT Checklist is shown in Additional file 1.

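### The primary chi-square test is valid but ignores baseline variables already known before allocation; prespecified covariate adjustment would give a modest gain in precision

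*Protocol article*

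**What the plan says.** All references are to the protocol article.

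- **Data analysis plan.** The primary analysis is by intention to treat: "The primary outcome, live birth rate, will be compared between the two groups using the Pearson chi-square test". The threshold is given as "A two-sided alpha level of 0.05 will be considered statistically significant". Women lost to follow-up count as having no live birth. The section names no covariate for this comparison.
- **Sample size.** "we assume that the live birth rate will be improved from 35% in the sET arm to 60% in the pET arm", with "a statistical power of 1 − *β* = 0.80" and a two-tailed 5% test. The result is 59 women per arm, raised to 66 per arm (132 in all) for 10% dropout.
- **Randomization and blinding.** Allocation follows a "computer-generated dynamic block randomization sequence" with blocks of 2, 4 and 6. No stratification factor is named. Allocation is revealed on the day of biopsy, and doctors are not blinded.
- **Inclusion criteria.** A woman may enter after three or more failed transfers of good-quality embryos, or after two or more failed euploid blastocyst transfers. Age at oocyte retrieval must be 20-39.
- **Screening.** "The history of previous fertility treatments" is recorded, and this explicitly covers embryo transfers.

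**The concern.** Age at retrieval, the number of earlier failed transfers and the way a woman met the RIF definition are all known before allocation, and each could plausibly predict live birth. The article's own Discussion attributes failed implantation to embryo quality, endometrial receptivity or both. Women whose earlier failures involved untested embryos may therefore have a different outlook from women whose euploid embryos failed, now that everyone receives a single euploid blastocyst.

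With 66 women per arm and no named stratification, these features can be unevenly spread by chance. The unadjusted test allows for this in its error rate but makes no use of what is known about it. What is at stake is precision: a somewhat wider interval and somewhat lower power than the same data could give.

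**Working it through.** **Inputs.** From Sample size: 35% v 60%, 1:1 allocation, two-sided 0.05, power 0.80, 59 then 66 per arm, 10% dropout. Assumed: R², the share of within-arm outcome variance that the covariates explain. The document gives no value, so a range is shown.

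**1. The plan's own figure.** With unpooled variance, n = (1.960 + 0.842)² × (0.35×0.65 + 0.60×0.40) / 0.25² = 7.849 × 0.4675 / 0.0625 = 58.7, so 59 per arm. Then 59 / 0.9 = 65.6, so 66 per arm and 132 in all. Both stated figures reproduce.

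**2. The planned test.** The pooled form that matches Pearson's chi-square is power = Φ{[Δ√n − 1.960√(2p̄(1−p̄))] / √(p₁q₁ + p₂q₂)}. At n = 66 and p̄ = 0.475 this is Φ{[0.25×8.124 − 1.960×0.706] / 0.684} = Φ(0.946) = 82.8%. Exact enumeration gives 81.8%. At 59 per arm the values are 78.4% and 79.2%. Exact type I error, checked at common rates of 35% and 47.5%, lies between 4.5% and 5.2%.

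**3. Adjustment.** Adjusting scales the variance by (1 − R²), so n is replaced by n/(1 − R²). For R² of 0.05 and 0.10, 1/(1 − R²) is 1.05 and 1.11, equivalent to 5% and 11% more women.

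**4. Dropouts counted as failures.** If all 10% of dropouts count as no live birth and would otherwise have had the planned rates, the rates become 0.9×35 = 31.5% and 0.9×60 = 54.0%. In the last column R² refers to the outcome as analysed; dropout unrelated to the covariates would dilute it somewhat.

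| R² (assumed) | 59 per arm, 35 v 60 | 66 per arm, 35 v 60 | 66 per arm, 31.5 v 54 |
|---|---|---|---|
| 0 | 78.4% | 82.8% | 74.9% |
| 0.05 | 80.4% | 84.7% | 77.0% |
| 0.10 | 82.5% | 86.6% | 79.3% |
| 0.15 | 84.7% | 88.4% | 81.5% |

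**5. RIF entry alone.** For a two-category covariate, R² = f(1−f)D² / 0.23375, where f is the share of women in one category, D the difference in live birth between categories, and 0.23375 the mean of 0.2275 and 0.24. With f = 20-50% and D = 10-20 points (assumptions), R² runs from 0.16×0.01/0.23375 = 0.007 to 0.25×0.04/0.23375 = 0.043. Power at 66 per arm is then 83.1% to 84.4%, a gain of 0.3 to 1.6 points.

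**6. Simulation.** A logistic model standardised to a risk difference was compared with the chi-square, 4,000 trials per setting. Chi-square v adjusted at 59 per arm:
- R² = 0 with five useless covariates: 77.8% v 77.1%
- R² = 0.03: 78.4% v 78.5%
- R² = 0.07: 79.0% v 81.5%
- R² = 0.14: 78.8% v 83.8%

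Null rejection rates were close for the two methods at 59 per arm. At 66 per arm the adjusted gains looked larger (83.1% v 86.2% at R² = 0.07). There, however, the chi-square rejected less often under the null (4.3% v 5.4%), so the results at 59 per arm are the fairer comparison.

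**7. Chance imbalance and the interval.** The standard error of the risk difference at 66 per arm is √(0.4675/66) = 8.4 points. The part due to covariate imbalance has SD √R² × 8.4, which is 1.9 points at R² = 0.05 and 2.7 at R² = 0.10. The 95% half-width is 1.96 × 8.4 = 16.5 points unadjusted and 15.6 at R² = 0.10.

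**The case against.** The strongest defence is that nothing is broken. The chi-square tests the same two-proportion contrast that sized the trial, its error rate is correct, and pooling two RIF definitions in a randomised comparison does not bias it. All of that stands.

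The benefit depends on an R² found nowhere in the document, and eligibility already narrows the prognostic spread: age 20-39, a good-quality euploid blastocyst, single transfer, and exclusion of cavity disease, thin endometrium and recurrent loss. That also stands. It argues for the lower end of the range, and RIF entry alone is worth under 2 points.

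A reader might take the lack of a stated effect measure or interval as a defect. The document does not support that: this is a journal article, such details are commonly left to an analysis plan that is not shown, and the promised counts and percentages by arm let anyone compute a risk difference and its interval.

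Two practical objections also stand. The RIF conditions overlap, since a woman with three failed good-quality euploid transfers meets both, so a simple route variable would be undefined. And more than 72 women had been recruited at submission, with doctors unblinded, so a change of primary analysis needs protection against the charge of choosing it after seeing results.

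None of this removes the point. The unadjusted test is a stated choice, and a more efficient one is available from data already recorded.

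**Conclusion.** The point holds as a modest improvement to a valid primary analysis. At 66 per arm, adjustment would raise power from about 83% to 85-87% if the covariates explain 5-10% of outcome variance, or from about 75% to 77-79% if all 10% dropouts count as no live birth. The realistic range is about 0 to 4 points gained. If the covariates prove useless, the cost is under 1 point (0.7 in the simulation at 59 per arm).

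A reader might infer more: that the chi-square is invalid, that mixing RIF definitions biases the result, or that adjustment recovers lost power for free. The document supports none of these. Before the failure rule is applied, the design meets its 80% target within tolerance. The drop to about 75% comes from counting dropouts as failures, not from the lack of adjustment, and restoring 80% there would need R² of about 0.12.

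The gain rests on the assumed R²; the validity and baseline power of the planned test do not.

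**What to change.** By a dated amendment made before any outcome data are compared by arm:

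- Prespecify a logistic regression of live birth on arm, age at oocyte retrieval, number of previous failed transfers, and a non-overlapping indicator of RIF entry, for example two or more failed euploid blastocyst transfers, yes or no.
- Standardise it to a marginal risk difference with 95% CI. A conditional odds ratio would change the quantity being estimated; the standardised difference stays on the 35% v 60% scale used for the sample size.
- Report the Pearson chi-square alongside as the unadjusted analysis.

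No new data are needed. The costs are the wording, a few lines of code, a possible loss of under 1 point of power, and documenting a mid-trial change. Because doctors know the allocation, the amendment should record that no outcome comparison by arm had been made. If one has already been made, the adjusted result should be labelled post hoc and the chi-square kept as primary.

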## Discussion

This is a trial aiming to evaluate the potential benefits of personalized embryo transfer, based on the endometrial receptivity testing, on live birth rate among patients with RIF undergoing FET after PGT-A. We plan to enroll 132 subjects from an academic reproductive center in China. The enrollment began in August 2021 and is expected to end in June 2024. The result of this RCT will provide high-quality evidence on the efficacy of ERT in predicting the WOI and improving pregnancy outcomes for patients with RIF. We assume that pET based on ERT will improve the live birth rate in patients with RIF.

RIF is a complex and challenging clinical condition in the field of ART. The failure of embryo implantation can be attributed to a variety of factors, including embryo quality, endometrial receptivity, or both [29, 30]. In the past few decades, many interventions have been proposed to improve embryo quality or endometrial receptivity, including techniques such as PGT-A to improve embryo selection, hysteroscopy to assess the uterine cavity, parental karyotype analysis to rule out chromosomal abnormalities, and screening for endocrine, immunological, and thrombophilia factors that may impact implantation [6, 30]. Additionally, synchronization between the endometrium and the embryo is another critical factor involved in successful implantation. Displacement of WOI has been suggested as one of the primary causes of failure for a euploid embryo to implant [31]. With the development of high-throughput omics, an increasing number of studies have focused on the discovery of gene expression related to endometrial receptivity [18, 20–22]. A novel endometrial receptivity testing technology based on RNA-Seq was thereby developed to uncover endometrial receptivity biomarkers through transcriptome analysis and to predict the ideal WOI [19].

However, clinical evidence regarding the effect of ERT remains limited. Only two clinical studies have been identified on this topic. He et al. conducted a prospective observational study including 142 women with RIF; results showed that WOI displacement was observed in 30.4% of cases, WOI narrowing was observed in 58.8% of cases, and pET based on ERT substantially increased the rate of intrauterine pregnancy (63.6% vs. 40.7%, *p* = 0.111) compared to that of sET when transferring blastocysts [19]. Additionally, Chen et al. reported similar findings in a retrospective study using propensity score matching, demonstrating that ERT-guided pET could significantly improve clinical pregnancy (50.0% vs. 16.7%, *p* = 0.001) and live birth rates (42.9% vs. 14.3%, *p* = 0.004) compared to pinopode-guided pET [23]. It should be noted that both studies were conducted in a non-randomized setting; thus, the efficacy of ERT needs to be further validated through well-designed randomized trials.

Thus, the purpose of the present study is to conduct a prospective, randomized, single-blind, clinical trial in patients with RIF and to evaluate the effect of ERT on live birth rate. Women with at least three unsuccessful good-quality embryo transfer cycles or two euploid embryo transfer cycles will be enrolled because we intend to include women who are more likely to have decreased endometrial receptivity and WOI displacement, so they can potentially benefit from ERT. To further minimize the confounding factors related to embryo quality, we have elected to include only participants who have undergone PGT-A treatment and have at least one good-quality euploid blastocysts for transfer. The results of this trial will provide high-quality evidence of the efficacy of ERT in the treatment of RIF.

Furthermore, it is also important for further research to consider the economic implications of ERT, including direct costs associated with the testing procedure, additional costs related to the testing cycle, and long-term economic implications of this intervention. Thorough cost-effectiveness analyses are necessary to inform decision-making regarding the adoption of ERT in clinical practice.

## Trial status

The study enrollment began in August 2021 and is expected to end in June 2024. The follow-up will continue and data collection will be completed in June 2025. At the time of the manuscript submission, the enrollment is ongoing, and more than 72 women have been recruited. The trial protocol is version 2.1, dated 25 March 2023.

## Data Availability

The datasets generated and processed during the current study are available from the corresponding author upon reasonable request.

## Abbreviations

AE: Adverse event
ART: Assisted reproductive technology
CBC: Complete blood count
ChiCTR: Chinese Clinical Trial Registry
CONSORT: Consolidated Standards of Reporting Trials
CRF: Case report form
DCC: Data Coordinating Center
ERA: Endometrial receptivity array
ERT: Endometrial receptivity testing
FET: Frozen embryo transfer
hCG: Human chorionic gonadotropin
HRT: Hormone replacement therapy
IQR: Interquartile ranges
ITT: Intention-to-treat
IVF: In vitro fertilization
pET: Personalized embryo transfer
PGT-A: Preimplantation genetic testing for aneuploidy
RCT: Randomized controlled trial
RIF: Recurrent implantation failure
RNA-Seq: RNA sequencing
SAE: Serious adverse event
SD: Standard deviation
sET: Standard embryo transfer
WOI: Window of implantation
